**Figure 3 F3:**
[figure not shown]
Graphs showing the impact of base SSI rate and rate of unrelated infections on the required sample size. SSI, surgical site infection.

### Recruitment

We estimate that with only one centre, such as Danderyd Hospital, recruitment would take >5 years. The hospital operates about 4500 patients each year and as it is unlikely that more than 500 of these will be excluded. We, therefore, anticipate recruiting 4000 patients/year. Performing this study in a multicentre setting is, therefore, crucial. In table 1, the participating centres are presented, and their estimated proportion of patients included.

### Patient and public involvement

Representatives of the Swedish Osteoporosis Society (www.osteoporos.org) and the Swedish Rheumatic Society (www.reumatiker.se) are members of the study steering committee, and participate mainly in discussions regarding plans for reporting and publishing the results of the study.

## Methods: an assignment of interventions

### Allocation

The three PAP devices in each OR will synchronically be randomised in periods of 4 weeks, 6 weeks or 8 weeks to either have the system ‘on’ or ‘off’. The switch will always occur midnight Friday in order to limit the patients exposed to partial effect during the first 2 days after switching status. The system can be programmed to be active (ie, plasma chamber eradicating bacteria) at any given timeframe. The manufacturer of the PAP devices will prepare the randomisation allocation and automatic execution of it. The randomisation sequence is at minimum 8 years long and will be submitted to a third, independent party, responsible for keeping the allocation secret until interim analyses or study end. At the interim analyses, only allocations up to that date will be released.

### Blinding

The on/off only refers to the plasma chamber responsible for the antimicrobial effect. As the machine retains the air flow it will be impossible for staff, surgeons and patients to determine the status of the machine from the outside. The device will also automatically switch status, where the true status is concealed for all study participants, including other hospital personnel until the end of the study.

## Methods: data collection, management and analysis

### Data collection methods

For the primary endpoint, the following codes will be used to detect if individual patients have contracted an SSI following surgery. If any of these codes indicate SSI, a chart review will be performed in a second step to verify the outcome:

From the Swedish PDR: withdrawal of antibiotics targeting *S. aureus* corresponding to a minimum amount of two defined daily dosages (an estimate provided by the registry for the expected daily dosage). The date of withdrawal will serve as an indicator of treatment start unless inpatient data are available with more granular information. The drug Anatomical Therapeutic Chemical (ATC) codes considered to target relevant bacteria are:J01CF05 (isoxazolylpenicillin).J01FF01 (clindamycin).J04AB02 (rifampicin).From The National Patient Registry: ICD trigger codes indicating postoperative infections:T793: posttraumatic wound infection, not elsewhere classifiedT814: infection following a procedure, not elsewhere classifiedT84[5-7]: infection and inflammatory reaction due to internal joint prosthesis, internal fixation device or other internal orthopaedic prosthetic devices, implants and graftsT874: infection of amputation stumpB9[5,6,8]: bacterial specificationL0[2-4]: cutaneous abscess, furuncle and carbuncle, and cellulitis.A[24]6: erysipeloid and erysipelasFrom the National Patient Registry: NOMESCO trigger codes indicating postoperative infections:Incision abscess: TN[A-H]05Surgeries due infections: N[A-H]S[0–4,9]9.Extremities wound revision: Q(CD)B05.Reoperation for infection: N[A-H]W69.Vacuum treatment: DQ023.

Both local and national registry data will be used according to availability. For the admission episodes with the code indicators, the admission date is the index date, that is, if an admission occurs after 91 days with a trigger code it will not be considered an indicator of a postoperative infection.

In-hospital information systems will supply information on: (1) patient ID, (2) date(s) of surgery, (3) surgery associated codes, including operated side, (4) OR and (5) in-hospital antibiotics

Both the surgical and medical data records will be retrieved depending on availability. Only centres that can provide the above data will be allowed to participate.

The Swedish National Patient Register includes all in-patient care and outpatient visits in Sweden with discharge codes according to ICD-10, NOMESCO codes and admission/discharge dates.^26^

The Swedish PDR includes any withdrawn prescriptions. Prescriptions that are never withdrawn by patients and drugs bought over the counter without prescriptions are not included. The data fields used were the drug ATC code, number of pills and prescription text.^27^

### Data management

The study data will be securely managed and stored encrypted at a computer within Karolinska Institutet at Danderyd Hospital. No other than the authors stated above will gain access to raw data.

### Statistical methods

The primary outcome is a binary variable where there are three groups. We will use logistic regression where the reference group is the placebo group, and the significance is related to the intervention group. The estimate for the mixed group is only for relating dose effect, that is, the group will not be pooled with either the placebo or the intervention group. Due to the randomisation, we do not intend to have any other covariates as confounders in the model. Similar methodology will be applied to the antibiotic’s binary outcome. The number of days with antibiotics will be modelled using a linear regression with the similar interpretation to above regarding predictors. Mortality will be modelled using a Cox proportional hazards model with time since surgery calculated as time to death, migration or 2 years. The Cox model will not contain any covariates due to the randomised study nature. The analysis will be performed by an epidemiologist/statistician in our team (MG) and will be performed as a per-protocol analysis.

We will handle confounding by including only the patient’s first surgical procedure. The randomisation process will handle other confounding such as confounding by selection. Procedural confounding will be handled by the external part who has done the randomisation procedure for each PAP device. Regarding dropouts, the healthcare registers and chart review done in the study will ensure a very low (<1%) drop-out rate. Individual patients can also request that they are excluded from the registers and thus from the study, but by experience, this is very rare and will also not affect our ability to analyse our primary and secondary endpoints.

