The effect size of the primary endpoint is the relative risk of contracting SSI for the intervention group versus the control group and will be calculated by dividing the probability of contracting an SSI in the intervention group by the control group=$\frac{SSIrateinterventiongroup}{SSIratecontrolgroup}$. The effect size will also be presented as an absolute risk difference=SSIrateinterventiongroup−SSIratecontrolgroup.

The primary outcome is a surrogate variable for SSI as it, due to the large sample size, is practically impossible to have all patients come back for outpatient visits and be visually inspected. To further validate the outcome, a medical record review will be performed in a second step on all individual patients with indication of SSI. Our expectations are that the choice and succeeding validation of this proxy variable can provide us with a reliable tool for investigating SSI’s in future projects.

The Swedish healthcare registers, especially the Prescribed Drug Register (PDR) and the Patient Register, will make sure that we get an almost complete (>99%) coverage of all relevant SSIs.

The secondary outcomes are: (1) withdrawal or other documented use of any antibiotics for 2 days or more after surgery during the first 30 postoperative days, (2) the number of days with antibiotics during the first 30 days, (3) same as (1) and (2) but up to 90 days after surgery and (d) death during the first 2 postoperative years

These analyses will also be performed with and without adjustment for preoperative antibiotic use 6 months prior to the surgery.

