### Sample size

The reoperation rate in Sweden due to infections within the first 2 years after surgery is 1.3%^3^ for primary total hip replacements (THRs). This does not include THRs in patients with fracture and other types of surgeries that are more susceptible to infections. We, therefore, assume that the SSI rate in our study population is 2%.^1–3^ Similarly, we know from other data that about 0.7% withdraw the antibiotics associated with the primary outcome within a 3-month period prior to surgery. To account for infections unrelated to surgery, we assume that the infection noise rate, that is, non-SSIs, is less than 2%.

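### The primary test is a patient-level logistic regression that ignores the randomised OR-periods; the stated relative risk and risk difference should carry cluster-robust intervals and share one fit with the p value

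*Protocol article*

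**What the plan says.** Under Outcomes, the article fixes the measure: "The effect size of the primary endpoint is the relative risk of contracting SSI for the intervention group versus the control group", obtained as one group's rate divided by the other's. It adds: "The effect size will also be presented as an absolute risk difference".

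Under Statistical methods, it fixes the model. "The primary outcome is a binary variable where there are three groups" (intervention, placebo, and a mixed group for surgery within 2 days of a switch). It continues: "We will use logistic regression where the reference group is the placebo group, and the significance is related to the intervention group". On adjustment: "we do not intend to have any other covariates as confounders in the model". The approach carries over to the antibiotic endpoints: "Similar methodology will be applied to the" binary antibiotic outcome. Outcomes adds that analyses will be run with and without adjustment for antibiotic use in the 6 months before surgery.

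Under Allocation, the randomised unit is a period of 4, 6 or 8 weeks in one OR, whose three devices switch together. Every patient operated in that OR and period shares one assignment, apart from those in the 2-day window after a switch.

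The article mentions neither an odds ratio nor a confidence interval. It gives no step from the logistic fit to the RR or RD, and no term or variance adjustment for OR or period.

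**The concern.** Two things stand out when these sections are read together.

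The first is scale. The effect is defined on the risk scale, while the coefficient that is tested is a log odds ratio. The two statements need a link, so that the reported effect and its significance come from the same calculation.

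The second matters more. Assignment is made to OR-periods, but the stated model is an ordinary patient-level regression. Patients in one OR-period share staff, ventilation, case mix and season. If their outcomes are positively correlated for such reasons, a model-based standard error is too small, the p value is too small and any interval is too narrow. The trial may stop early on a significant result at its interim analysis, so the validity of the p value has a direct consequence.

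**Working it through.** **1. Reproduce the plan's own figure.** Inputs from Sample size: SSI rate 2%, noise rate up to 2%, 25% reduction, 80% power, alpha 0.05, 22 630 per group. With additive noise, control = 2.0% + 2.0% = 4.0% and intervention = 1.5% + 2.0% = 3.5%. The pooled two-proportion formula, two-sided, gives 22 663 per group; the arcsine version gives 22 639. Power at 22 630 is 79.9%. The figure reproduces, and it is a calculation for independent patients.

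**2. Does the scale matter for the primary outcome?** Take p1 = 0.040, p0 = 0.035 (control and intervention) and n = 22 630 per group, ignoring clustering.

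- RR = 0.035/0.040 = 0.875. SE(log RR) = √[0.960/(n×0.040) + 0.965/(n×0.035)] = 0.0477. 95% CI 0.797 to 0.961; z = -2.797.
- OR = (0.035/0.965)/(0.040/0.960) = 0.870. SE(log OR) = √[1/(n×0.040×0.960) + 1/(n×0.035×0.965)] = 0.0496. 95% CI 0.790 to 0.959; z = -2.798.
- RD = -0.50 percentage points. SE = √[(0.040×0.960 + 0.035×0.965)/n] = 0.179 points. 95% CI -0.85 to -0.15; z = -2.800.

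Without noise (2.0% v 1.5%), RR is 0.750 and OR 0.746, with z of -4.041 and -4.042. The hypotheses OR = 1, RR = 1 and RD = 0 coincide. The scale changes neither the test nor the sample size.

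**3. Can the logistic model deliver the RR and RD?** Yes. With three groups and no other covariate it is saturated, so its fitted probabilities equal the observed group proportions. Their quotient and difference are exactly the quantities defined under Outcomes, and the delta method gives intervals from the same fit.

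**4. What ignoring OR-periods could do.** Let D be the ratio of the true variance to the independent-patient variance. Then z becomes z/√D, and the true type I error of a nominal two-sided 5% test is 2[1 - Φ(1.96/√D)]. The article gives neither an intracluster correlation nor the number of ORs, so the D values are an assumption:

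| D (assumed) | Expected z at 4.0% v 3.5% | Type I error of naive test | RD 95% CI (points) |
|---|---|---|---|
| 1.0 | -2.80 | 5.0% | -0.85 to -0.15 |
| 1.1 | -2.67 | 6.2% | -0.87 to -0.13 |
| 1.25 | -2.50 | 8.0% | -0.89 to -0.11 |
| 1.5 | -2.28 | 11.0% | -0.93 to -0.07 |

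The expected z would fall to 1.96 in size at D = (2.7975/1.96)² = 2.04.

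**5. Are there enough clusters for a robust variance?** From 17 April 2017 (12 months before the interim date under Data monitoring) to 31 December 2021 is 1719 days, or 245.6 weeks. One OR running throughout contributes between 245.6/8 ≈ 31 and 245.6/4 ≈ 61 periods. Several ORs over several hospitals therefore give a large number of OR-periods.

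**6. Binary antibiotic outcomes.** The article gives no control risk, so a range is assumed. For a true RR of 0.85:

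- 20%: (0.17/0.83)/(0.20/0.80) = 0.82
- 30%: (0.255/0.745)/(0.30/0.70) = 0.80
- 40%: (0.34/0.66)/(0.40/0.60) = 0.77

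Once preoperative antibiotic use is added as a main effect, the model is generally no longer saturated. Its odds ratio is then conditional on that covariate, and it can differ from the unadjusted one even under perfect randomisation.

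**The case against.** The strongest reply is that there is no contradiction. Testing with logistic regression while reporting RR and RD is common, the covariate-free model reproduces both exactly, and the tests agree to the second decimal. The article states no interval for any measure, and the method for intervals is normally left to the full protocol or SAP. RR and RD are named for the primary endpoint only, and the antibiotic risks used above are assumed.

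Most of this stands. A reader might infer that the logistic model cannot deliver the stated effect sizes, or that the raw quotient can have no valid interval. The documents do not support either: step 3 disposes of the first, and a raw ratio or difference can carry a delta-method or cluster-robust interval. The absence of a stated interval is silence, not error. Nor can it be said that the antibiotic odds ratios will mislead, because the article does not say they will be read as risk ratios.

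It can also be said that clustering is independent of the link function. That is right: it is no argument against the logistic model. It is an argument about the standard error. The article gives the model in some detail, down to reference group and covariates, and as written that model leaves out the randomised unit. A further fair point is that each OR switches between on and off, so stable differences between ORs largely balance out. This limits the inflation but does not remove correlation specific to a period within an OR.

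**Conclusion.** The point holds for the variance and not for the link. The primary effect is defined as RR and RD and tested by a covariate-free logistic regression. That difference in scale is immaterial (0.875 v 0.870, the same null hypothesis, no change to 22 630 per group), and the model need not be replaced. What needs correcting is that the p value and any interval from the model as written treat patients as independent, although OR-periods were randomised. The size is unknown from the document. Under assumed variance inflation of 1.1 to 1.5, the naive type I error is about 6% to 11%. If there is no correlation within OR-periods, nothing is lost by the change.

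For the binary antibiotic outcomes the point is conditional: an odds ratio would depart from the RR if those outcomes are common, and their control risk is not given.

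**What to change.** In Statistical methods, keep the logistic regression and add the following:

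- The RR and RD defined under Outcomes are reported with 95% confidence intervals, as standardised risks from the logistic fit (a log-link model for RR and an identity-link model for RD would also serve).
- Standard errors are clustered by randomised OR-period.
- The primary p value comes from that same cluster-robust fit.
- The binary antibiotic outcomes, including the analyses adjusted for preoperative antibiotic use, are reported as RR and RD in the same way.

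The cost is a sentence or two of text and a few lines of code. OR and date of surgery are already among the data to be collected, and the allocation sequence supplies the period. No new data are needed. The downside is that intervals may be slightly wider.

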### Intervention

At each hospital, all ORs that perform surgery on orthopaedic patients will be equipped with three^3^ PAP systems each. The groups are defined as: intervention group: those operated where the PAP device has been turned on for at least 2 days prior to index surgery; control group: those where the PAP device has been turned off for at least 2 days prior to index surgery; and mixed group: those receiving surgeries in ORs within 2 days after the PAP device switches status. In the analysis we will also subgroup the study subjects according to measurements prior to study start into regular ORs (≥10 CFU/m^3^) and ultra-clean ORs (<10 CFU/m^3^).

PAP device status and function will be monitored continuously during the inclusion period through standardised manual controls every 3 months, and also at the end of the inclusion period by validating PAP device status retrospectively through memory card recordings in each device.

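### The mixed group's estimate cannot be read as a dose effect, because partial exposure is inseparable from day of surgery and both switch directions are pooled (minor)

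*Protocol article*

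**What the plan says.** All of this is in the protocol article.

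- **Intervention** defines three groups. The intervention group is "those operated where the PAP device has been turned on for at least 2 days prior to index surgery", the control group is "those where the PAP device has been turned off for at least 2 days prior to index surgery", and the mixed group is "those receiving surgeries in ORs within 2 days after the PAP device switches status". The mixed definition does not distinguish the direction of the switch.
- **Allocation** sets periods of 4, 6 or 8 weeks and fixes the switching time: "The switch will always occur midnight Friday in order to limit the patients exposed to partial effect during the first 2 days after switching status".
- **Statistical methods** uses logistic regression with three groups and placebo as reference. The significance test concerns the intervention group. On the mixed group it says "The estimate for the mixed group is only for relating dose effect", and that it is not pooled with either arm. On adjustment it says, citing the randomisation, "we do not intend to have any other covariates as confounders in the model". Similar methods are applied to the binary antibiotic outcome, and a similar reading of the predictors to the number of antibiotic days.

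**The concern.** A dose reading needs the mixed and placebo patients to differ, apart from chance, only in how much device exposure they had. Under the switching rule they also differ in when they were operated on. Randomisation decides whether a room is on or off in a given period. It does not decide whether a patient is operated on in the first two days after a switch or on some other day. The reason given for leaving out covariates therefore covers intervention versus placebo but not mixed versus placebo.

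The exposure itself is also not one quantity. A room that has just gone on and a room that has just gone off are on opposite paths, and nothing in the article fixes their proportions.

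At stake is what the trial can say about dose: a mixed-group estimate between, below or above the other two could arise with or without any device effect. The same reading carries over to the antibiotic outcomes.

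**Working it through.** **1. The plan's own figure.** The 22 630 per group reproduces if the composite rate is 2% SSI plus 2% noise in control (4.0%) and 1.5% plus 2% under intervention (3.5%). With two-sided 5% significance and 80% power, the standard two-proportion formula gives 22 663. Without the noise (2.0% versus 1.5%) it gives 10 795, which does not match. So 4.0% versus 3.5% is the planning contrast, with odds ratio (0.035/0.965)/(0.040/0.960) = 0.87. The mixed group plays no part in this calculation.

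**2. Calendar composition.** This needs only the article's figures and equal use of the three period lengths. One period of each length is 18 weeks: 90 weekdays and 36 weekend days, 126 days in all. Midnight Friday is read as the night into Saturday.

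| | Every boundary changes status | Half of boundaries change status |
|---|---|---|
| Mixed days | 6 (6/126 = 4.8%) | 3 (3/126 = 2.4%) |
| Weekend share of mixed days | 100% | 100% |
| Weekend share of on/off days | 30/120 = 25% | 33/123 = 27% |

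The article does not say whether status alternates or is redrawn each period, so both columns are shown.

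**3. Patients in the mixed group (assumed weekend volume).** Let w be the volume of a weekend day relative to a weekday. Then n = 45 000 × (mixed days × w)/(90 + 36w).

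- w = 0.10, half of boundaries: 45 000 × 0.3/93.6 = 144.
- w = 0.25, every boundary: 45 000 × 1.5/99 = 682.
- If weekends held as much as 20% of all surgery (w = 0.625), every boundary: 45 000 × 3.75/112.5 = 1500.

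**4. Apparent effect with no device effect (assumed weekend risk).** Let r be the weekend-to-weekday ratio of the composite rate and f the weekend share of placebo patients. The mixed rate is 0.04r and the placebo rate is 0.04(1 − f + fr). With half of boundaries changing, f = 33w/(90 + 33w), which is 0.035 at w = 0.10 and 0.084 at w = 0.25.

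| r (assumed) | Apparent odds ratio, mixed versus placebo |
|---|---|
| 0.8 | 0.80–0.81 |
| 1.25 | 1.24–1.25 |
| 1.5 | 1.47–1.50 |
| 2.0 | 1.92–2.01 |

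Worked case, r = 1.5 and f = 0.084: placebo 0.0417, mixed 0.060, odds ratio (0.060/0.940)/(0.0417/0.9583) = 1.47. At r = 1 the odds ratio is 1 and there is no bias from this source.

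**5. Switch direction.** If status acted at once, an all off-to-on mixed group would have a rate of 3.5%, an all on-to-off group 4.0%, and an even mix 3.75%. The position on the dose scale depends on a proportion the plan does not fix.

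**6. Precision.** Take 22 000 placebo patients at 4.0% and a mixed rate of 3.75%. SE(log OR) = √(1/e + 1/(n − e) + 1/880 + 1/21 120), with e = 0.0375n. For n = 144, e = 5.4 and the 95% interval multiplies and divides the odds ratio by 2.4. For n = 682, e = 25.6 and the factor is 1.5. For n = 1500, e = 56 and the factor is 1.3.

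**The case against.** Four points can be made in the plan's defence.

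- **The main comparison is untouched.** This stands in full. In a one-factor model with group indicators, the intervention-versus-placebo coefficient does not depend on the third level. A reader might infer that the mixed estimate will be used to support or undermine the main result. No hypothesis, secondary outcome or stopping rule in the article uses it, so that inference is not supported.
- **The bias is not demonstrated.** This also stands. A reader might infer that the estimate reflects calendar day and case mix instead of dose. The article does not show that. It says of the hip-replacement rate used for planning that "This does not include THRs in patients with fracture and other types of surgeries that are more susceptible to infections", but it says nothing about which days such surgery is done. It also excludes open fractures, traumatic wounds and infected sites, which removes some acute high-risk cases. What is shown is only that the two explanations cannot be told apart.
- **An even mix of directions could be an intermediate exposure on average.** That is possible, so it would go too far to say the group has no place on a dose scale. But the mix is not fixed, and an average of opposite paths is hard to interpret.
- **So few events are unlikely to mislead.** Partly right. With a few hundred patients the interval would usually include 1, and the estimate is not tested. That is equally a reason not to give it a dose interpretation.

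If midnight Friday means 00:00 on Friday, the slot becomes Friday and Saturday. The group is then not weekend-only, but it is still a fixed slot set against the whole week.

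**Conclusion.** The point holds, and it is minor. The definitions, the switching time and the covariate-free model together mean that the mixed-versus-placebo estimate cannot separate partial exposure from day of surgery and case mix, and that it pools opposite switch directions. This follows from the article's own text.

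The size and direction of any bias are unknown. The group sizes and odds ratios above rest on assumed weekend volumes, assumed weekend risk ratios and an assumed share of boundaries that change status. They show only that moderate day-of-week differences could match or exceed the whole planned effect (odds ratio 0.87), in either direction. Keeping the mixed group unpooled is sound. The primary intervention-versus-placebo comparison and the 22 630 per group are unaffected.

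**What to change.** In Statistical methods, keep the mixed group separate but delete the dose-effect interpretation, for the primary outcome and for the antibiotic outcomes that follow the same scheme. Report the group descriptively: number of patients and event rate.

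If a partial-exposure reading is wanted:

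- split the group into off-to-on and on-to-off using the device memory-card records;
- compare each part only with surgery on the same days of the week in settled-on and settled-off periods;
- state the expected number of events in advance, and label the result exploratory and imprecise.

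The cost is a sentence or two of analysis text. Surgery date, OR and device status are already collected, and the primary analysis loses no power. What is given up is a dose statement that the design cannot support.

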**Trial registration number:**

NCT02695368.

Strengths and limitations of this studyEPOS is a multicentre, placebo-controlled trial with approximately 45 000 study subjects, that will evaluate the effect of plasma air purification on the incidence of surgical site infections (SSIs) after orthopaedic surgery.The double-blinded design provides strong internal validity to the study results.The cluster-randomisation design, which is created through switching of the exposure within each operating room (OR), minimises the risk of allocation bias.This study is the first randomized controlled trial, to the best of our knowledge, investigating the true cause-and-effect relationship between an air-purifying intervention in ORs and SSIs.The primary limitation to the study is the resource intensity, mainly due to the large number of study subjects required to study such an unusual outcome, and the concomitant review of medical records to validate the outcome.

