#### Multicentre power with ultra-clean air

Hospitals with ORs with ultra-clean air may be less susceptible to the effect with an already lower infection rate. Pre-study CFU measurements suggest that approximately 80% of the included ORs are ultra clean. If we assume that the infection rate is 2% or less, and that the effect size is reduced to 25% in an ultra-clean environment, we will need to recruit 22 630 patients in each group, that is, approximately 45 000 patients to attain a power of 80% with a significance level of 0.05. This will be our target population. We expect a very low drop-out rate/missing data in the study, estimated to be <1%. At the interim analysis, the p value will be set 10 times lower at 0.005, that is, if a statistically significant result between the groups is observed at 18 months, the study will be stopped. See figure 3 and online supplemental appendix 1 for details in R and explanation of the script for the sample size analysis.

10.1136/bmjopen-2020-047500.supp1Supplementary data

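### The planned models treat patients as independently randomised although operating-room periods are randomised, so the p values and intervals hold only if correlation within those periods is negligible

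*Protocol article*

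**What the plan says.** The strengths and limitations list describes the design as "The cluster-randomisation design, which is created through switching of the exposure within each operating room". The Allocation section gives the unit: "The three PAP devices in each OR will synchronically be randomised in periods of 4 weeks, 6 weeks or 8 weeks". All patients operated on in one room during one block therefore share one allocation.

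The Statistical methods section then fixes the primary analysis: "We will use logistic regression where the reference group is the placebo group, and the significance is related to the intervention group". The model has a three-level factor (on, off, mixed) and nothing else: "Due to the randomisation, we do not intend to have any other covariates as confounders in the model". The binary antibiotic outcome is to be handled in a similar way, and days on antibiotics by a linear regression with similar predictors. For mortality, "The Cox model will not contain any covariates due to the randomised study nature".

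No random effect, generalised estimating equation, robust variance, or term for OR, hospital or period appears in the article. The sample size section mentions no intracluster correlation (ICC) and no design effect.

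**The concern.** The reason given for the plain model answers a different question. Randomisation removes confounding on average, whichever unit is randomised. The standard error must still reflect how many units were randomised and how similar patients within a unit are. Patients in the same room and block share staff, case mix, ventilation and season. The article itself expects risk to vary by room: it puts about 80% of the ORs in the ultra-clean class and says such rooms may already have fewer infections.

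The variance component decides what goes wrong:

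- Variation from block to block within a room makes the plain standard error too small, however status is assigned.
- Stable differences between rooms largely cancel if each room alternates on and off. If status is drawn afresh for each block, they inflate the error too. The Allocation section does not say which applies.

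At stake are the one primary test and the interim test at 0.005, which can stop the trial.

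**Working it through.** **1. The plan's own figure.** Inputs from the sample size sections: SSI rate 2%, relative reduction 25%, and unrelated infections below 2% (taken here as 2% in both groups). The criterion is "to attain a power of 80% with a significance level of 0.05". This compares p1 = 0.02 + 0.02 = 0.040 with p2 = 0.015 + 0.02 = 0.035, mean 0.0375.

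n per group = [1.96·√(2·0.0375·0.9625) + 0.842·√(0.04·0.96 + 0.035·0.965)]² / 0.005² = 22,663.

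The article states 22,630, a difference of about 0.15%. The formula for independent patients therefore accounts for the whole figure and leaves no room for a design effect. (Without the 2% noise it gives 10,795, which does not match.)

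**2. Assumed cluster structure.** The article gives neither the number of ORs nor an ICC, so both are assumptions. April 2017 to the end of 2021 is about 247 weeks, or about 41 six-week blocks per OR. With 40 ORs and 27 patients per block, 40 × 41 × 27 = 44,280 patients, close to the target. The event rate is 3.75%, the mean of the two arms.

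**3. Formula, OR-period variation alone.** With standard deviation (SD) s on the logit scale, ICC ≈ 0.0375·0.9625·s². The design effect is DE = 1 + (27 − 1)·ICC. The true type I error of the plain test is 2·[1 − Φ(1.96/√DE)].

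| OR-period SD | ICC | DE | Type I error at nominal 5% |
|---|---|---|---|
| 0.2 | 0.0014 | 1.04 | 5.4% |
| 0.3 | 0.0032 | 1.08 | 6.0% |
| 0.5 | 0.0090 | 1.23 | 7.8% |

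**4. Simulation of the same layout with no treatment effect.**

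- OR-period SD 0.2–0.3 alone: 5.5–6.0%.
- OR-period SD 0.5 alone: about 8%.
- OR-period SD 0.5 plus between-OR SD 0.5: about 9–11%. The upper end needs independent draws per block. With alternating status and the average event rate held at 3.75%, it stays at 8.0–8.2%.
- Between-OR SD 0.3–0.5 alone: near nominal with alternating status; 5.3–8.2% with independent draws.
- OR-clustered robust variance: about 4.6–5.9% in every scenario.

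**5. Sensitivity to the assumptions.** By the formula in step 3, 70 ORs (about 16 patients per block) with ICC 0.0005 give 5.1%. At the other end, 15 ORs (about 73 per block) with ICC 0.01 give DE 1.72 and 13.5%.

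**6. Interim test.** The nominal 0.005 corresponds to z = 2.807. With DE 1.18 (30 ORs, about 37 patients per block, ICC 0.005) the true level is 2·[1 − Φ(2.807/√1.18)] = 0.0098. With DE 1.36 (same layout, ICC 0.01) it is 0.016. The strict threshold is thus inflated proportionally more than the final one.

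**The case against.** Four points can be made for the plan.

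- **The sentence is about confounders.** It declines covariates as confounders and does not literally forbid a robust variance or a random effect. This is a condensed article, and an analysis plan may exist. That is fair as far as it goes. But the article does name the model, leaves everything else out and gives a reason, and nothing signals a cluster-aware variance.
- **The design is forgiving.** Each room switches many times, so stable room and hospital differences largely cancel if status alternates. This stands, and it limits the harm. It does not remove the effect of block-to-block variation.
- **The inflation may be trivial.** With 15–27 patients per block and an ICC of 0.001, type I error is 5.2–5.3%. An OR-period SD of 0.5 is a strong assumption: infection odds in the same room would range from about 0.38 to 2.7 times the average. This stands. A reader might infer that the p value and interval are certainly wrong, or that error rates of 9% or more follow from OR-period variation of that size alone. The documents support neither: no ICC or number of ORs is given, and such rates need differences between rooms as well, or much larger blocks.
- **The effect measure.** A reader might also infer a contradiction because a logistic model yields an odds ratio while the Outcomes section says: "The effect size of the primary endpoint is the relative risk of contracting SSI for the intervention group versus the control group". That section obtains the relative risk and the risk difference directly from the two group rates, and at 4.0% versus 3.5% the relative risk is 0.875 and the odds ratio 0.870. No error of substance follows. What is missing is an interval for those measures that respects the clustering.

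**Conclusion.** The point holds in conditional form. As written, the analysis does not follow the randomisation, and the justification offered for it is mistaken. The plain standard errors are right only under an assumption about correlation that the article neither states nor supports, and the sample size rests on the same assumption.

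The existence of the mismatch is certain. Its size is not. In the 40-OR layout the excess over 5% runs from under one percentage point (OR-period SD 0.2) to about three points (SD 0.5). It reaches four to six points only when large differences between rooms are added. Fewer rooms, and so larger blocks, would raise these figures; more rooms would lower them. The change is still needed, because one test decides the trial, the interim test can end it early, and a valid analysis is available from data already being collected.

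**What to change.** Analyse in line with the randomisation. Either keep the group-only model with robust variance clustered on OR and a small-sample correction, or fit random effects for OR and OR-period. Apply the same choice to the primary, interim, secondary binary, antibiotic-days and Cox analyses. Give the relative risk and the risk difference cluster-aware confidence intervals. Keep the unadjusted model as a sensitivity analysis.

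If robust variance is used, cluster on the OR rather than the OR-period. With alternating status and stable differences between rooms (15 ORs, between-OR SD 0.4), OR-period clustering was conservative, rejecting in about 2.7% of simulated trials at nominal 5%. It would also help to state whether status alternates or is drawn independently for each block. Terms for OR class or calendar time, or a different link function, are optional and not needed to repair this point.

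The cost is a revised paragraph and a few lines of code. The Data collection methods section already lists OR and date of surgery among the items supplied. Intervals would widen slightly: by √DE, about 2% at OR-period SD 0.2 and 11% at SD 0.5 in the assumed layout.
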